### FOBT

We will use an immunological latex agglutination test (OC Sensor, Eiken, Tokyo, Japan), performed on a single stool sample with no dietary restrictions imposed on the participant, with the positivity cut-off set at 100 ng/ml. All FOBT samples collected in each study location will be shipped weekly to a single central laboratory and processed (automated processing and reading) in accordance with the manufacturer’s instructions. Participants with a positive test will be contacted by the study staff and offered an appointment date for a colonoscopy. A standard response letter will be mailed to participants with a negative result.

### Complications

Any complications that arise during screening (CTC or FS), or immediately afterward, will be reported in the examination record. Complications of CTC or FS that occur within 30 days after the procedure will be recorded through the linkage with hospital discharge records and mortality registers. All complications will be detailed according to type, timing, severity, treatment, and outcome. Information about subsequent complications will be collected through self-report telephone questionnaire administered 1 month after the examination. In addition, we will search the regional hospital discharge databases to check for any hospitalizations possibly related to screening test complications.

### Follow-up and management of polyps

#### FS

All participants will be informed about the results of their examination on the day of the procedure. If any small polyps (<10 mm) have been removed, histology assessment of tissue samples will be used to provide a definitive diagnosis and participants will be informed about the results within 2 weeks. Colonoscopy will be offered to any participants with advanced adenomas (that is, one adenoma ≥ 10 mm, or high-grade dysplasia, or villous component >20%), or with three or more adenomas of any type. Participants with a negative FS result or with hyperplastic polyps or ‘low-risk’ adenoma (that is, <2 tubular adenomas with low-grade dysplasia and smaller than 10 mm) will not undergo further follow-up.

#### CTC

If CTC reveals at least one lesion of 6 mm (C-RADS grade 2) or larger (C-RADS 3 to 4), the participant will be contacted by telephone and invited to undergo colonoscopy [37]. Participants whose examintion is inadequate according to the reporting radiologist, either because of poor bowel preparation, poor distension, or presence of artifacts, will be invited by telephone to undergo FS. Participants with no colonic lesions or with polyps smaller than 6 mm at CTC will be classified as negative, and informed of their result by regular mail. This cohort of participants will be scheduled for invitation to undergo a FOBT after 2 years. Participants with relevant extracolonic findings (that is, grade E4 and aortic aneurysms >4 cm) will be contacted by telephone and invited to the radiology unit of their nearest participating center for further investigations [37]. Extracolonic diseases that have already been diagnosed prior to CTC will be excluded from further assessments.

#### FOBT

All participants with a negative FOBT test will receive a letter notifying the result, and an indication to repeat the test after 2 years. All participants with a positive FOBT result will be invited by telephone to undergo colonoscopy.

#### Second-level colonoscopy

Second-level colonoscopy will be performed at the endoscopic unit of each participating center, using 130 cm colonoscope and air insufflation. Bowel preparation consists of a low-fiber diet starting 3 days before the examination and by the oral intake of 2 liters of polyethylene glycol solution (Moviprep; Norginey) followed by 2 liters of clear liquids the afternoon before examination. No standard protocol for sedation will be introduced. However, all centers will be required to discuss with the participant the advantages and drawbacks of performing sedated colonoscopy. Colonoscopy will be considered complete if the cecum is visualized or, in the case of failure, if a subsequent colonoscopy performed within 6 months after the index one is able to reach the cecum. The combined results of the two examinations will be included in the analysis. All detected lesions will be measured with open biopsy forceps and annotated according to their size, macroscopic appearance (sessile, pedunculated, non-polypoid, vegetating, stenosing), and location (rectum, sigmoid, descending, transverse, ascending, cecum).

#### Pathology

Histology will be defined according to the Word Health Organization criteria [54]. Advanced adenoma will be defined as an adenoma with any of the following features: size 10 mm or larger, high-grade dysplasia, or a villous component of more than 20%. Cancer will be defined as the invasion of malignant cells beyond the muscularis mucosae. Participants with intramucosal carcinoma or carcinoma *in situ* will be classified as having high-grade dysplasia. Participants will be classified on the basis of their most advanced lesion in order to determine the prevalence of pathological features. Polyp size will be classified according to the diameter of the largest polyp; for each polyp, we will use the largest measure indicated by either the endoscopist or pathologist.

### Questionnaires

#### Acceptability of the screening tests

The efficiency of CRC screening depends upon participants accepting and being able to complete the recommended procedures [55]. Therefore, we will investigate several issues related to the proposed screening tests, using questionnaires administrated at three time points to all participants in the CTC and FS groups. First, a short itemized questionnaire evaluating discomfort due to bowel preparation for the procedure will be administered immediately before CTC and FS. After completing the procedure, a second questionnaire assessing discomfort, pain, and embarrassment experienced during the procedure will be administered. A third questionnaire investigating all aspect of the screening procedure will be administered by telephone interview 1 month after the examination.

#### Reasons for participation or non-participation

Evaluation of factors associated with participation or non-participation in a new screening program is an essential component of this project. To understand the reasons for participation or non-participation, a structured questionnaire will be administered by telephone to a sample of individuals (both attendees and non-attendees) who were invited to the study 2. This will assess demographic and socioeconomic status, self-reported health status, beliefs about the benefit of screening, attitude to having regular medical control, perception of CRC risk, adoption of health-promoting behaviors (for example, physical activity, smoking habits). Factors including medical advice about CRC, knowing a close relative or friend with CRC, and experience of previous examinations for early CRC detection or for other preventive tests (for example, mammography/PAP test for women, prostate testing for men) will be evaluated. Included items are drawn from an existing questionnaire [56]. Both attendees and non-attendees will be asked to indicate their main reason for accepting or refusing screening. Non-attendees will be asked to indicate factors that might possibly induce them to undergo screening in the future, and to answer questions investigating their knowledge of aspects of the screening process as described in the leaflet (for example, bowel preparation, duration of examination).

#### Cost-effectiveness analysis

This trial includes a full economic evaluation to examine the relative cost-effectiveness of CTC screening compared with FS screening and with no screening. Cost-effectiveness analysis will be evaluated by incorporating the trial data into a previously validated screening model [33]. The advantage of this analysis is that we will collect cost data prospectively as part of the present screening trial, including the direct costs (related to provision of a diagnostic screening service) and the private costs to subjects of participation in the study, such as travel costs, out-of-pocket expenses, and costs of productivity loss. Direct costs will include cost of investigating the CTC colorectal and extracolonic findings, and the costs of screening-induced complications. In detail, the yearly CTC cost will be determined by separately collecting data relative to the following costs: 1) medical/non-medical staff; 2) initial and maintenance costs for CTC and colonoscopy equipment; 3) disposable material for CTC and colonoscopy; 4) hospital furniture for CTC and colonoscopy; 5) histological analysis of colonoscopy-detected lesions; 6) other costs (for example, investment in IT). These yearly costs will therefore be divided by the estimated number of CTC screenings to be performed in 1 year, in order to calculate the cost of each CTC screening test. The effect of CTC examination on the quality of life (QOL) of the participants will be indirectly estimated by the questionnaires assessing the degree of satisfaction and anxiety, which will be administered after CTC screening completion. It is beyond the scope of this study to assess the QOL of any participants diagnosed with cancer, because of the very small number of cancers expected in each arm. Furthermore, the cost-effectiveness analysis will take into account the effects on health-related QOL (or health status) from the process of screening for CRC, such as pain, physical discomfort, or feelings of anxiety or emotional distress. This analysis may provide important information for larger-scale CRC screening programs using CTC.

### Ethics approval

Approval for the study has been granted by the local Ethics Review Committee in each clinical site: Comitato Etico dell'Azienda Ospedaliera Universitaria S. Luigi Gonzaga di Orbassano; AO Città della Salute e della Scienza di Torino; Comitato Etico Interaziendale AOU ‘Maggiore della Carità`,’ ASL Biella, ASL Novara, ASL Vercelli, ASL VCO; Comitato Etico Regina Margherita-Sant'Anna-Ordine Mauriziano; amd Comitato Etico della Provincia di Verona.

### Data analyses

The primary endpoint of the study 1, the detection rate of the screening test, is defined as the proportion of screened subjects with advanced neoplasia divided by the total number of screened subjects. Advanced neoplasia comprises all cancers and advanced adenomas together. The most advanced detected lesion per screened subject will be used to calculate the detection rate. The overall prevalence of polyps of any histology will also be calculated. Detection rates and detection rate differences will be calculated, and all proportions will be reported with 95% confidence interval (CI). Differences in proportions between screening strategies will be calculated using the χ^2^ test. Multivariate logistic regression models with advanced neoplasia as a function of sex, center, and screening test will be used to analyze the differences in detection rate between screening tests. Odds ratio (OR) and its 95% CI will be used as a measure of the association between detection and the variables under evaluation. As a secondary analysis, we will calculate referral rate for each screening test, defined as the proportion of screening tests referred for colonoscopy because of an abnormal result. For the comparison topic, we will use the number of diagnostic colonoscopies induced by each screening test as a proxy for resource utilization and costs.

The primary endpoint of study 2, the participation rate for the screening test, is defined as the number of participants undergoing the screening test relative to the total number of invitees. The χ^2^ test will be used to test if the CTC group achieves a statistically significant difference in participation compared with the FS group. Multivariate models will be fitted to the data, with participation as a function of sex, screening test, and sociodemographic characteristics. All statistical tests will be two-sided and considered statistically significant at *P* < 0.05.

### Sample size

#### Comparison with endpoint of screening detection (study 1)

Based on the data from the Screening Colon Retto (SCORE3) trial [53], the overall prevalence of advanced neoplasia (advanced adenomas and CRC) in the target age range is assumed to be 5% at FS screening. By including 5,000 participants in the study (2,500 in each screening group), we will achieve a statistical power of 80% to detect a 2% difference in detection rate between the FS and CTC groups (5% versus 7%), using the conventional 5% (two-tailed) level of statistical significance. Assuming an adherence to the study of about 25%, we plan to invite 20,000 eligible individuals. This assumption is based on data from the SCORE3 trial [53].

#### Comparison with endpoint of adherence to screening invitation (study 2)

We plan to invite 1,000 individuals for screening with FS, under the assumption that 25% of those invited will accept the invitation [53]. Another 1,000 individuals will be invited for screening with CTC. Thus, it will be possible to detect as statistically significant an absolute difference in participation rates of more than 5% with a one-tailed test, setting the value of the alpha error equal to 5% (power = 80%).

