**Figure 1 F1:**
[figure not shown]
Design of the screening trial comparing detection rates of advanced neoplasia between computed tomography colonoscopy (CTC) and flexible sigmoidoscopy (FS) as primary colorectal cancer (CRC) screening tests.

For study 2, an additional 2,000 individuals aged 58 years living in Turin, Italy and who are listed in GP rosters will be randomly assigned to receive an invitation for screening with CTC or FS (Figure 2). In the FS arm, non-responders will be randomized subsequently to receive an invitation for screening with CTC or FOBT at 6 months from the initial invitation. In the CTC arm, non-responders will be offered FOBT as an alternative screening test. Simple randomization will be performed by personnel of the Center for Cancer Prevention (CPO) in Piedmont, Turin, using a computer-generated allocation algorithm, with an allocation ratio of 1:1.

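### Study 2 is sized with a one-tailed test but will be analysed two-sided, so power for a 5-point participation difference is about 71%, not 80%

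*Protocol article*

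**What the plan says.** The protocol article's section on sample size for adherence to the screening invitation (study 2) gives these inputs:

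- FS arm: "We plan to invite 1,000 individuals for screening with FS", "under the assumption that 25% of those invited will accept the invitation".
- CTC arm: "Another 1,000 individuals will be invited for screening with CTC".
- Claim: "Thus, it will be possible to detect as statistically significant an absolute difference in participation rates of more than 5% with a one-tailed test", with an alpha error of 5% and power of 80%.

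The Study design section gives the allocation for study 2 as 1:1.

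The Data analyses section defines participation as people screened divided by all people invited. It names a chi-square test for a difference between the CTC and FS groups and closes the same paragraph with "All statistical tests will be two-sided and considered statistically significant at" P < 0.05. It does not exempt study 2. The study 1 sample size is calculated at a two-tailed 5% level.

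**The concern.** The sample size section and the analysis section specify different tests for the same primary endpoint. The stated power belongs to a one-tailed 5% test, and the declared analysis is two-sided at 5%, which has less power for the same numbers. The article gives no reason for treating study 2 differently from study 1.

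Two things are at stake. First, participation is the primary endpoint of study 2 and part of the trial's primary objective. Readers of a non-significant result would believe that a true 5-point difference had a 20% chance of being missed, when the chance is higher. Second, the rejection rule is open to two readings. A result in favour of CTC with a one-sided P value of 0.03 would be significant under the sample size section and not under the analysis section.

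A one-tailed test in favour of CTC could also not declare lower CTC uptake. That outcome is conceivable on the protocol's own description of the preparations: three days of diet and laxative for CTC, against a single enema without dietary restriction for FS.

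**Working it through.** **Inputs.** n = 1,000 per arm, FS uptake p1 = 0.25, difference d = 0.05, alpha = 0.05 and target power 0.80, all from the study 2 sample size section. Two-sided testing comes from Data analyses. The direction of the difference is not stated, so both are computed. The denominator is all invitees, so no allowance for dropout is needed.

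**Formula** (normal approximation to the chi-square test, pooled variance under the null):

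- SE0 = sqrt(2 × pbar × (1 − pbar) / n), where pbar = (p1 + p2)/2
- SE1 = sqrt((p1(1 − p1) + p2(1 − p2)) / n)
- power = Φ((d − z × SE0) / SE1), with z = 1.645 one-sided or 1.960 two-sided

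**Step 1: reproduce the stated 80%, taking 25% versus 30%.**

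- pbar = 0.275; SE0 = sqrt(2 × 0.275 × 0.725 / 1,000) = 0.01997
- SE1 = sqrt((0.1875 + 0.2100) / 1,000) = 0.01994
- one-sided: (0.05 − 1.645 × 0.01997) / 0.01994 = 0.860, so power = 80.5%
- the matching sample size for 80% is 986 per arm, close to the 1,000 planned

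The figure reproduces, so the inputs are read correctly. One-sided 25% versus 20% would give 85.0% (862 per arm), so an increase to 30% is the case that matches the text.

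**Step 2: the same inputs with the declared two-sided test.**

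- (0.05 − 1.960 × 0.01997) / 0.01994 = 0.545, so power = 70.7%
- type II error = 100% − 70.7% = 29.3%
- sample size for 80%: (1.960 × sqrt(0.39875) + 0.842 × sqrt(0.3975))² / 0.05² = 1,251 per arm, or 2,502 in total

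**Step 3: the other direction, 25% versus 20%, two-sided.**

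- pbar = 0.225; SE0 = 0.01867; SE1 = 0.01864
- (0.05 − 1.960 × 0.01867) / 0.01864 = 0.719, so power = 76.4%; 80% needs 1,094 per arm

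**Step 4: sensitivity to the formula.**

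| Comparison | Test | Pooled | Unpooled | Arcsine | Continuity-corrected |
|---|---|---|---|---|---|
| 25% v 30% | one-sided | 80.5% | 80.6% | 80.5% | 79.1% |
| 25% v 30% | two-sided | 70.7% | 70.8% | 70.8% | 69.0% |
| 25% v 20% | two-sided | 76.4% | 76.5% | 76.5% | 74.7% |

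**Step 5: difference detectable at 1,000 per arm with 80% power, two-sided.** Solving the power formula for d gives +5.6 points (25% to 30.6%) or −5.2 points (25% to 19.8%). The corresponding one-sided figures are +5.0 and −4.7 points.

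**Step 6: where the two rules disagree.** With SE0 = 0.01997, the one-tailed rule rejects above 1.645 × 0.01997 = 3.3 points and the two-sided rule above 1.960 × 0.01997 = 3.9 points. An observed CTC excess of roughly 3.3 to 3.9 points would be significant under one section only.

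**The case against.** The best case on the other side has five parts.

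- *The 80% is correct on its own terms.* It is. The defect is that those terms are not the terms of the planned analysis.
- *The 71% depends on direction.* This stands as a qualification. The article states no direction, and for a fall to 20% two-sided power is 76.4%. But only the increase to 30% reproduces the stated 80%, and neither direction reaches 80%. The wording about differences of more than 5 points does not help either, since power stays below 80% up to 5.6 points upward or 5.2 downward.
- *A directional test is defensible.* The Background and Discussion give some grounds for expecting better uptake with CTC, while the heavier bowel preparation points the other way. Whether a one-tailed test suits the question is therefore arguable, and the finding does not rest on it. If a one-tailed test was intended, the Data analyses section is the one in error and a correction is still needed.
- *A null result is judged by its confidence interval, not by planned power.* This is right. Near 25% uptake the 95% interval for the difference has a half-width of about 1.96 × sqrt(2 × 0.25 × 0.75 / 1,000) = 3.8 points, so an observed difference near zero would exclude 5 points in any case. What remains is the misstated chance of missing a true 5-point difference.
- *The consequence is modest.* The two-sided test still controls type I error, and study 1 is unaffected. That makes the correction cheap, but it does not make the stated power of a primary endpoint correct.

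**Conclusion.** The concern holds. The stated 80% power for study 2 applies to a one-tailed 5% test, and the protocol commits to two-sided testing without exception. For the 25% versus 30% comparison that reproduces the stated figure, power under the declared test is about 71% (69% with continuity correction), and the risk of missing the difference rises from 20% to 29%. For 25% versus 20% that risk is about 24%. These figures assume 25% FS uptake, exactly 1,000 invitees per arm and independent responses. They change little with the choice of approximation.

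**What to change.** Keep the two-sided chi-square test and the 2,000 invitees. In the study 2 sample size section, replace the one-tailed claim with a statement along these lines:

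*With 1,000 invitees per arm, FS participation of 25% and a two-sided 5% test, power is about 71% for 25% versus 30% and about 76% for 25% versus 20%; 80% power is reached for an increase of about 5.6 points or a decrease of about 5.2 points.*

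Because recruitment has been under way since December 2010, it is reasonable to add that the number of invitees was chosen on a one-tailed calculation, so that the record stays honest. Make the change before the study 2 outcome is analysed, so that the choice of sidedness cannot follow the data.

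The cost is one sentence and a slightly less favourable stated power. There are two alternatives. Restoring 80% power for a 5-point increase under the two-sided test needs about 1,251 per arm, which is 2,502 − 2,000 = 502 more invitees. Keeping the one-tailed test would require a stated justification, a stated direction and an explicit exception in the Data analyses section.

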## Discussion

FS is currently recommended for population screening programs in Italy, and is used in several regions [57]. CTC is a possible alternative to FS. To date, prospective data about the effectiveness (CRC incidence/mortality reduction) of CTC in comparison with FS for population-based screening are lacking. Moreover, several issues concerning CTC implementation as a mass screening program deserve to be addressed: patient compliance with CTC (implying reduced bowel preparation), radiologist reading times, radiologic workload, organizational impact, and economic costs. Randomized trials are clearly needed to test this novel screening approach and develop infrastructures capable of maximizing the advantages and minimizing the burden of CTC use in screening, favoring its feasibility and cost-effectiveness.

In Europe, several RCTs on the use of CTC as a CRC screening strategy have been implemented or are about to be implemented [25,40]. In these studies, CTC is compared with FOBT screening or colonoscopy as a first-level test. Our results and those of the aforementioned studies will provide national and regional health system authorities with crucial information and experience on the utility of CTC technology in CRC screening programs.

This RCT is designed to compare the detection rate of CTC for advanced neoplasia versus FS. Detection of advanced neoplasia (measured in each screening arm as the detection rate of advanced neoplasia among all participants) has been universally adopted as a crucial endpoint when validating CRC screening techniques [58]. One challenge of a trial that has detection as the primary endpoint is that the outcome assessment can be systematically influenced by selection and/or confounding biases. A RCT does not guarantee comparable groups, because selection and confounding biases may arise as a result of human interference in the recruitment procedures. For example, participants who agree to receive CTC may be systematically different from participants in the FS arm because of medical or family histories or lifestyle choices that may be associated with a different likelihood of colorectal adenomas at screening [59]. This may lead to systematic differences in the presence of advanced neoplasia between the screening arms, affecting the results of the study and their validity. Thus, we have attempted to reduce this form of bias by using a design in which only participants without strong preferences for one screening test will be randomized to the screening arms. In fact, participation in the trial is restricted to individuals who consent to randomization. Although this approach avoids confounding and should allow scientifically accurate conclusions about screening detection, it also hinders recruitment, and precludes the possibility of evaluating adhesion to CTC invitation in comparison with that to FS. However, adhesion to screening invitation is a crucial determinant of the effectiveness of a screening program. Consequentially, the evaluation of participation in a screening program should be in place before any program implementation has begun. To achieve this objective, we designed a second RCT, in which eligible individuals are randomized without consent to receive one of the two screening tests. Furthermore, this second trial makes it possible to collect data on reasons for participation or non-participation. Understanding the reasons behind participation and non-participation can be of help in the development of interventions aimed at increasing uptake of screening for CRC.

When comparing FS and CTC as CRC screening strategies, an important issue needs to be considered. FS-detected polyps 6 mm or smaller can be removed immediately, whereas such lesions are usually ignored during CTC screening. Because the long-term implications of removing diminutive polyps are unknown, long-term follow-up of very large samples would be required to estimate the protection of CTC screening against death. To our knowledge, no such trials are planned or ongoing. However, our study will provide indirect evidence of the long-term benefit from CTC screening by comparing the detection rates for CTC versus FS and assuming long-term efficacy of FS screening consistent with the results from the SCORE trial [9]. Of note, the SCORE trial evaluated the protection for FS screening over time in the same screening setting.

One more issue we kept in mind while planning the trial is that overall costs of CTC screening could be affected by uncritical reporting of extracolonic findings [37]. Whether the visualization of extracolonic structures and potential pathology is a real benefit or a disadvantage is still under debate. On the one hand, CTC may incidentally identify asymptomatic malignant diseases or other clinically important conditions, thus possibly reducing mortality. On the other hand, CTC may reveal numerous findings of no clinical relevance, which could result in costly additional diagnostic examinations with an overall negative impact on cost-effectiveness [39]. However, in some cases, detection of relevant extracolonic findings such as abdominal aortic aneurysms (AAA) and extracolonic masses at an early stage may be beneficial. According to one study, the net effect from detection of both AAAs and extracolonic cancers appears to be positive in term of life-years gained and overall cost-effectiveness [38]. Furthermore, cost-effectiveness analyses have also shown that screening for AAA provides high clinical efficacy at a relatively low cost [60]. Based on these considerations, we decide to report and follow only potentially important extracolonic findings such as abdominal and pelvic masses, and AAA larger than 4 cm, which represent only a minority of all extracolonic findings. This study will provide new knowledge on this topic through a separate analysis of the additional costs created by referring patients wtih important extracolonic findings for second-level tests.

In this trial, we are implementing a telediagnosis model for CTC reading, which consists of performing the examinations in different regional hospitals and sending data via telematic infrastructures to a central unit where the CTC examinations are interpreted by experienced radiologists. It is hoped that this organizational model will ensure high diagnostic quality, as it enables reporting to take place in a protected environment by a board of dedicated radiologists with certified experience in CTC. The use of a telediagnosis model may also favor adherence to CTC invitation thanks to the local availability of radiological centers that can perform examinations. A comprehensive evaluation on cost-efficiency of a telediagnosis model for CRC screening by CTC will include all these aspects.

In this trial, we are using the DR FR-CAD reading paradigm. In our preliminary work, we showed that this new reading modality is just as accurate as second reader CAD, but is less time-consuming [51]. It is hoped that this RCT will confirm the results of these preliminary findings.

In summary, this RCT will assess the efficacy of a CRC prevention program with CTC as a mass screening strategy in some regions of Italy, providing information about adherence, detection rate, and costs of this test compared with FS. In addition, the collection of data for cost-effectiveness analysis as part of this RCT will help to capture important aspects of CTC screening, such as adverse effects on QOL, resource use, and indirect costs. Thus, this trial will provide relevant information to decision-makers who need to consider evidence of economic value along with clinical efficacy when making decisions on resource allocation.

